#### Inclusion criteria

Cancer services will be eligible to participate if they provide care for at least 100 patients per year in NSW Australia. Eligible cancer services may operate within the public or private healthcare system. They may be whole services or single departments within services, such as tumour streams (e.g. breast cancer or haematology) or treatment streams (such as medical or radiation oncology). If there is more than one department/hospital which shares common staff members, they will be considered one site for the purpose of this study. This is necessary to ensure that participating staff members are not exposed to both Core and Enhanced implementation strategies.

#### Exclusion criteria

Cancer services will be excluded if they are unable to commit to:endorsing and enabling staff training for ADAPTengaging with ADAPT staff for the 3-month engagement and tailoring periodallowing a complete site profile audit and release of their organisational chartauthorising release (with individual patient consent) of Medical and Pharmaceutical Benefit (MBS/PBS) provider information and statistics;and if they do not have Wi-Fi/broadband/internet access and/or an internet browser version that complies with the ADAPT Portal requirements.

#### Recruitment: cancer services and staff

An initial meeting (face to face or via teleconference) will be held, attended by representatives of the ADAPT research team, the Head of the cancer service, and representatives of the psychosocial, nursing, clinical trial and IT staff. At this meeting, the study will be described in detail, and potential interest in participation will be ascertained. Interested cancer services will be asked to identify a local ADAPT champion, and to sign an ADAPT Research Participation Agreement.

All staff employed on a permanent or ongoing (6 months or more) basis, either full or part time or as a visiting medical officer, in a role that provides clinical care to patients with cancer or client focussed administrative support or IT/managerial support, will be invited to participate in the study. Staff will be identified as part of the organisation chart mapping exercise during site engagement. Site champions will identify and approach eligible staff, to whom they will explain the study. Interested staff will be contacted by the research team and provided with a written information sheet and consent form to sign.

A site, or individual cancer service staff member, may withdraw from the study and elect to have their data removed from the study database. If a site chooses to withdraw prior to completion of baseline data collection, and there is sufficient time within the study timeline, the site will be replaced by a reserve list site pre-randomised to the same study arm.

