### Interventions/groups

Sites will be randomised to a Core implementation arm versus an Enhanced implementation arm to facilitate uptake of the ADAPT CP. All cancer services will receive access to, and training to support use of, the online resources developed to support ADAPT. These resources (described in detail above) are the:ADAPT PortalADAPT Health professional trainingADAPT Patient education materialsiCanADAPT Cognitive-behavioural Therapy

The Core implementation and Enhanced implementation arms will differ in the implementation strategies used to support the use of ADAPT CP at their cancer service. Specifically, these differences are:*Core:* These sites will receive implementation strategies consistent with usual roll out of a clinical pathway in the NSW health context, to inform staff of the ADAPT CP and enable them to initiate use of the ADAPT Portal and intervention resources. Once the ADAPT Portal is launched and the implementation phase has commenced, Core sites will receive reporting feedback and audit reports at 4 weekly intervals and additional support from the ADAPT team only at their request (a passive approach).*Enhanced:* These sites will receive the same implementation strategies as the core group, with the addition of more prolonged, active engagement of the ADAPT team, that will continue during the 12-month implementation phase. These additional strategies will include monthly meetings to identify training and support needs of local champions, additional awareness activities, audit and feedback reports prior to and midway through the implementation phase summarised and presented face-to-face by research staff to site staff, and other tailored strategies to address the specific barriers and facilitators in each site (an active approach).

The strategies, described in detail in Table 1, were developed by the research team, comprising experts in the fields of psycho-oncology and implementation science, cancer services leaders, and consumers. A literature review, NSW Health current implementation practices, and the ADAPT barriers and enablers study [23] guided the development of the strategies.

**Table 1 Tab1:** Implementation strategies

Strategy	Both Core and Enhanced implementation strategies arms	Enhanced implementation strategies arm *only*

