Awareness campaign	• Roadshow presentation by ADAPT staff at the site 8 weeks before “go-live” • Poster displayed prominently 4 weeks prior to and at “go-live,” (T0) • Email from site champion to all staff 1 week before “go-live” (T0)	• Additional posters at 4-monthly intervals during implementation • Newsletters emailed to site staff at 2, 4, 6, 9 and 12 months
Champions	• Champion identification and role definition • Provision of email templates for champion to send staff • Inclusion of champion contact details in all staff communication	• Additional proactive contact with Champions at monthly intervals to discuss progress, provide audit reports and discuss additional implementation strategies as needed
Academic detailing and support	• Sites provide with a written report summarising change readiness data from baseline staff interviews at T0 • Tailoring of the ADAPT Portal to site requirements during engagement meetings • Study close meeting with all key staff to discuss sustainability of the ADAPT CP	• Sites provided with a verbal report of these data, at T0, T1 and T2 • Quarterly review of ADAPT Portal configuration to confirm allocated responsibilities and service tailoring
Reporting	• Monthly written reports on Portal statistics	• Presentation and highlighting of issues from monthly reports in face-to-face meetings with site
Technological support	• IT support for the ADAPT Portal	

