### Measures

#### Primary outcome

The primary outcome is site adherence to the ADAPT CP, operationalised as the percentage of patients at each site whose care is considered adherent to the ADAPT CP, using data extracted from the ADAPT Portal. The measure, guided by the literature on adherence [30], captures for each patient, whether they received the ADAPT CP components (screening, triage conversation, referral, referral uptake check, progress review, discharge summary, and rescreening) appropriate for their level of anxiety and depression, expressed as a continuous score of 0–100. Mean scores will be calculated for each site, averaging scores for all patients. This continuous mean score will be transformed into a binary score of adherent (≥70% of patients experiencing ≥70% of appropriate components) or non-adherent (< 70% of patients experiencing ≥70% of appropriate components), based on accepted implementation targets [31, 32].

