### Statistical methods

#### Sample size and justification

##### Power for primary endpoints

Based on cancer registry data for NSW (2009) (https://www.cancerinstitute.org.au/data-research/data-held-by-cinsw/nsw-cancer-registry), approximately 37,525 patients in NSW will be diagnosed with cancer in NSW each year. Based on prior epidemiological studies, 42–45% and 35–37% of these will experience mild depression or mild anxiety, respectively [3, 36, 37] and 22–36% and 20–30% will experience moderate to severe depression and/or anxiety respectively.

Based on incidence and prevalence of cancer in NSW, a conservative estimate of 464 screening events per site (total sample of 5568 screening events in 12 sites), there is at least 80% power to detect a difference in adherence rates of 30% in the Core and 60% in the Enhanced arm using a two-tailed test with Type 1 error rate of 5%. The sample size has been adjusted for the variance inflation factor due to the clustered design and can accommodate an intraclass correlation coefficient (ICC) as high as 0.14 to achieve 80% power and 0.10 to achieve 90% power [38, 39]. Although estimates of the ICC are not available, we expect the ICC will be within this range. Based on the Cancer Institute figures, we do not envisage any difficulty in recruiting the required sample for this study. Note that the number of screening events and projected sample size and power may be revised based on screening at the first three services.

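### A randomised site may withdraw and have its data removed, with no stated limit protecting the Portal data behind the primary outcome

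*Protocol article*

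**What the plan says.** Under Recruitment: cancer services and staff, the protocol article states: "A site, or individual cancer service staff member, may withdraw from the study and elect to have their data removed from the study database". The next sentence is the only time-bound one, and it governs replacement, not deletion: "If a site chooses to withdraw prior to completion of baseline data collection, and there is sufficient time within the study timeline", a reserve site already randomised to the same arm takes the place.

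Under Primary outcome: "The primary outcome is site adherence to the ADAPT CP", scored patient by patient "using data extracted from the ADAPT Portal".

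On what sites see during the 12 months, Table 1 gives both arms "Monthly written reports on Portal statistics". The Interventions/groups text adds that "Core sites will receive reporting feedback and audit reports at 4 weekly intervals". Enhanced sites alone also receive "Presentation and highlighting of issues from monthly reports in face-to-face meetings with site".

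The sample size section plans 12 sites of 464 screening events and adjusts for clustering. It names no allowance for lost sites.

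**The concern.** The site is the unit of randomisation. On a plain reading, a site's own data include its Portal record, so the rule lets a whole randomised cluster leave the primary comparison, including outcomes already collected. Nothing elsewhere in the article narrows this.

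Two features make the loss more than a nuisance. First, sites get regular information on their Portal activity, so a site that is struggling can probably tell, and the decision to leave may be related to adherence. Enhanced sites have the issues in those reports pointed out face to face and Core sites do not, so any such tendency need not be equal in the two arms. Second, no replacement is provided for after baseline, so the arm analysed would no longer be the arm randomised. With so few clusters, one removal can affect both the precision and the estimate.

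**Working it through.** **Inputs.** From the sample size section: 12 sites, 464 screening events per site, 30% (Core) against 60% (Enhanced), two-sided 5%, ICC up to 0.14 for 80% power and up to 0.10 for 90%. Assumed, because the article gives no allocation ratio: six sites per arm, of equal size.

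**1. Reproduce the plan's figure.** Design effect = 1 + (464 − 1) × ICC, which is 65.82 at ICC 0.14 and 47.30 at ICC 0.10. Effective number per arm = 6 × 464 / 65.82 = 42.3 and 6 × 464 / 47.30 = 58.9. With the pooled-variance normal formula,

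power = Φ{ [|p₂ − p₁| − 1.96 √(p̄(1 − p̄)(1/n₁ + 1/n₂))] / √(p₁(1 − p₁)/n₁ + p₂(1 − p₂)/n₂) }.

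At ICC 0.14: (0.30 − 1.96 × 0.1082) / 0.1031 = 0.853, so power is 80.3%. At ICC 0.10 power is 91.5%. The required total at ICC 0.14 is 2 × 42 × 65.82 = 5529, against 5568 stated. The plan's figures reproduce and are not in dispute.

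**2. Lose one site, for any reason.** Effective number in the depleted arm at ICC 0.14 = 5 × 464 / 65.82 = 35.2.

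| Sites analysed | Power, ICC 0.14 | Power, ICC 0.10 |
|---|---|---|
| 6 v 6 | 80.3% | 91.5% |
| 5 v 6 | about 76% | 88.8% |
| 5 v 5 | 72.6% | 85.9% |
| 4 v 6 | about 71% | 84–85% |

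A t reference with sites − 2 degrees of freedom starts lower but falls by a similar amount: 74.6% for 6 v 6 and 69–70% for 5 v 6 at ICC 0.14.

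**3. Lose the lowest adherer of one arm.** The expected minimum of six standard normal values is about −1.27, so the mean of the other five rises by 1.27 / 5 = 0.25 between-site SD. Between-site SD = √(ICC × p(1 − p)).

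- ICC 0.05: SD is 0.102 (p = 0.3) or 0.110 (p = 0.6), a shift of 2.6 to 2.8 points.
- ICC 0.14: SD is 0.171 or 0.183, a shift of 4.4 to 4.7 points.

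**4. Check by simulation.** Beta-binomial sites, 40,000 trials per setting, unweighted t-test on site means. With no true effect:

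| ICC | Adherence, both arms | Two-sided error, all sites kept | Shift, lowest Enhanced site removed | Two-sided error then | Of which favouring Enhanced |
|---|---|---|---|---|---|
| 0.10 | 30% | 5.1% | +3.4 points | 7.8% | 6.6% |
| 0.10 | 60% | 4.9% | +4.1 points | 7.8% | 6.5% |
| 0.14 | 30% | 4.9% | +3.9 points | 7.9% | 6.7% |
| 0.14 | 60% | 5.3% | +4.9 points | 8.0% | 6.7% |

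Removing the lowest Core site instead gives the mirror image. If both arms lose their lowest site, the shift cancels, but two-sided error at ICC 0.14 is still 7.6% to 8.2%, because trimming narrows the apparent between-site spread.

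With the planned effect, removing the lowest Enhanced or the lowest Core site turns a 30.0-point difference into 32.9 or 27.5 points at ICC 0.05, and 34.9 or 26.0 points at ICC 0.14.

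**The case against.** **Omission.** This is a condensed article. Analysis sets and the handling of withdrawals commonly sit in a full protocol or analysis plan, and the site agreement is not shown. That is right as far as it goes, and the absence of an analysis-set definition is not the point. The deletion right is a stated rule, and no analysis plan can analyse data that have been removed.

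**Scope of the site's data.** The article does not say whether Portal records of routine care count as a site's own data. The plain reading includes them, but this is an ambiguity. It stands as a reason to clarify.

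**Staff members.** A reader might infer that a staff member's withdrawal would erase that person's logged Portal actions and make delivered care look missing. The documents do not support this. What staff supply is described as questionnaires and interviews, and the data-collection text below Table 2 separates staff surveys from the data collected through the Portal. Staff withdrawal therefore bears on secondary outcomes and predictors, and an individual's right to withdraw personal research data is ordinary.

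**Knowledge of the outcome.** A reader might also infer that sites know their primary result when they decide. The reports are described as Portal statistics and audit feedback. They are not said to show the adherence score, which Table 2 schedules at 6 and 12 months. Performance-related withdrawal is possible, but it is not established.

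**Magnitude.** The bias and error figures require a site to leave after baseline, choose deletion and be the lowest of its six. No probability is attached to these steps. ICC 0.14 is the most the design tolerates at 80% power, not an expected value. The planned analysis is a bias-corrected GEE at patient level, not a t-test on site means. Sites also differ in size, so one site need not hold a sixth of its arm's patients. All of this stands, and the figures should be read as conditional.

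**Conclusion.** The point holds for sites. The protocol permits a randomised cluster to be removed from the primary comparison after randomisation, with no stated time limit and no protection for the Portal data.

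The more general consequence is lost precision: about 4 points of power for one unreplaced site at ICC 0.14, assuming six equal sites per arm. The more serious consequence is conditional. If the lowest adherer in one arm is the site deleted, the difference moves by roughly 2.5 to 5 points in that arm's favour across ICC 0.05 to 0.14, against a planned 30 points, and two-sided type I error rises from about 5% to about 8%. The direction cannot be predicted, because either arm could lose the site.

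The figures do not mean that the trial as planned runs at an 8% error rate. They show what the rule would allow in an unfavourable but possible case.

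**What to change.** Amend the withdrawal sentence under Recruitment: cancer services and staff, and carry the same terms into the Research Participation Agreement and the staff information sheet:

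- A site that withdraws stops study activities (implementation strategies and further surveys). Its Portal data up to withdrawal are kept and analysed in its randomised arm.
- Where the site agrees, the automated Portal extract continues to month 12.
- Data removal applies only to an individual staff member's own questionnaire and interview data.
- Each site withdrawal is reported with arm, date and reason, with a sensitivity analysis for missing clusters.

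This leaves staff members' rights over their own data intact, and it avoids discarding records of patients who did not themselves withdraw.

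It does not fully restore the all-sites figures above. If extraction stops at withdrawal, patients registered shortly before may lack later components such as progress review and rescreening, so some bias and power loss can remain.

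The cost is a wording change in three documents and no extra instruments. Some sites may be slightly more reluctant to sign.

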#### Recruitment: patients

All patients at participating sites receiving psychosocial care related to their cancer diagnosis will be treated according to the ADAPT CP as part of routine care during the 12-month implementation period. If a patient does not wish to complete screening on a particular occasion (defer) or declines screening completely, this will be recorded in the ADAPT Portal and noted within the patient’s medical record, in line with usual record keeping practices at participating cancer services.

Patients participating in the ADAPT CP will be asked to give informed consent for the researchers to access their medical records and/or Medicare and Pharmaceutical Benefits Scheme (MBS/PBS) claims history for a period of 10 years to enable health economic analyses. Patients may withdraw this consent at any time.

### Interventions/groups

Sites will be randomised to a Core implementation arm versus an Enhanced implementation arm to facilitate uptake of the ADAPT CP. All cancer services will receive access to, and training to support use of, the online resources developed to support ADAPT. These resources (described in detail above) are the:ADAPT PortalADAPT Health professional trainingADAPT Patient education materialsiCanADAPT Cognitive-behavioural Therapy

The Core implementation and Enhanced implementation arms will differ in the implementation strategies used to support the use of ADAPT CP at their cancer service. Specifically, these differences are:*Core:* These sites will receive implementation strategies consistent with usual roll out of a clinical pathway in the NSW health context, to inform staff of the ADAPT CP and enable them to initiate use of the ADAPT Portal and intervention resources. Once the ADAPT Portal is launched and the implementation phase has commenced, Core sites will receive reporting feedback and audit reports at 4 weekly intervals and additional support from the ADAPT team only at their request (a passive approach).*Enhanced:* These sites will receive the same implementation strategies as the core group, with the addition of more prolonged, active engagement of the ADAPT team, that will continue during the 12-month implementation phase. These additional strategies will include monthly meetings to identify training and support needs of local champions, additional awareness activities, audit and feedback reports prior to and midway through the implementation phase summarised and presented face-to-face by research staff to site staff, and other tailored strategies to address the specific barriers and facilitators in each site (an active approach).

The strategies, described in detail in Table 1, were developed by the research team, comprising experts in the fields of psycho-oncology and implementation science, cancer services leaders, and consumers. A literature review, NSW Health current implementation practices, and the ADAPT barriers and enablers study [23] guided the development of the strategies.

**Table 1 Tab1:** Implementation strategies

Strategy	Both Core and Enhanced implementation strategies arms	Enhanced implementation strategies arm *only*
Awareness campaign	• Roadshow presentation by ADAPT staff at the site 8 weeks before “go-live” • Poster displayed prominently 4 weeks prior to and at “go-live,” (T0) • Email from site champion to all staff 1 week before “go-live” (T0)	• Additional posters at 4-monthly intervals during implementation • Newsletters emailed to site staff at 2, 4, 6, 9 and 12 months
Champions	• Champion identification and role definition • Provision of email templates for champion to send staff • Inclusion of champion contact details in all staff communication	• Additional proactive contact with Champions at monthly intervals to discuss progress, provide audit reports and discuss additional implementation strategies as needed
Academic detailing and support	• Sites provide with a written report summarising change readiness data from baseline staff interviews at T0 • Tailoring of the ADAPT Portal to site requirements during engagement meetings • Study close meeting with all key staff to discuss sustainability of the ADAPT CP	• Sites provided with a verbal report of these data, at T0, T1 and T2 • Quarterly review of ADAPT Portal configuration to confirm allocated responsibilities and service tailoring
Reporting	• Monthly written reports on Portal statistics	• Presentation and highlighting of issues from monthly reports in face-to-face meetings with site
Technological support	• IT support for the ADAPT Portal	

### Study procedures and timeline

Randomisation will be performed by the study statistician using online randomisation software (STATA). Allocation concealment will be preserved; both sites and ADAPT Program staff conducting assessments will remain blinded until study completion. Following randomisation, sites will undertake a 3-month period of engagement to clarify study procedures, train staff in the ADAPT CP and use of the ADAPT resources, and tailor the ADAPT Portal to local site resources and preferences. Study sites will then complete baseline (T0) staff questionnaires and interviews to ascertain staff views on service and staff readiness to adopt the ADAPT CP. The online questionnaires will be available on RedCap (Research Electronic Data Capture) [29] and automatically downloaded to a database to reduce possible bias. The ADAPT research team will follow-up those participants who do not complete or return their questionnaire within 2 weeks, with up to three reminder emails or phone calls at different times of the day. A subset of staff with key roles in implementing the ADAPT CP will be invited to participate in an audio-recorded semi-structured interview exploring their views of the ADAPT CP, barriers and facilitators to its use and site readiness.

Sites will then “go-live,” integrating the ADAPT CP into clinical care for a 12-month implementation period. Staff will be encouraged to introduce the ADAPT CP to all patients as part of routine care, and on their verbal consent, register them into the ADAPT Portal. Patients will then be asked to access the ADAPT Portal for efficient screening and data collection, information and access to ADAPT resources. Staff will be asked to respond to ADAPT emails and alerts for patients who require further assessment and referral. ADAPT research staff will administer Core versus Enhanced implementation strategies as per randomisation during this period.

Mid-way through the 12-month implementation period (T1 at 6 months) and at the end of the implementation period (T2 at 12 months), questionnaire data will again be collected from cancer service staff, and a subset of cancer service staff will participate in an audio-recorded semi-structured interview to ascertain staff views on implementation outcomes, and awareness of and perceived utility of the ADAPT CP implementation strategies.

Timing of enrolment, engagement, intervention and data collection is shown in Table 2.

**Table 2 Tab2:** Schedule of enrolment, engagement, intervention and data collection

		Study period					
	Enrolment	Engagement	Allocation	Intervention			Costs retrieval
Timepoint	-T2	-T1	0	T0 “Go-live”	T1 6 mths	T2 12 mths	T3 3 mths post
Enrolment:							
Eligibility Screen	X						
Informed Consent	X						
Governance	X						
Engagement:							
Role definition		X					
Tailoring		X					
Staff training		X					
Allocation			X				
Interventions:							
Core				X	X	X	
Enhanced				X	X	X	
Assessments:							
Primary outcome							
Adherence: CP					X	X	
Secondary outcomes							
Acceptability				X	X	X	
Adoption					X	X	
Appropriateness				X	X	X	
Feasibility				X	X	X	
Costs				X	X	X	X
Penetration					X	X	
Sustainability						X	
ORIC, Hands4U, study-developed organisational readiness items				X	X	X	
Demographic & disease items				X			

Case report forms (CRFs) in this study will take the form of site profile forms, contact logs, implementation strategy checklist and observational diaries, implementation strategy data psycho-social activity data and Medicare Data forms completed by ADAPT Program staff to collect service level data and staff surveys completed by cancer service staff participants. All other quantitative data will be collected electronically via the ADAPT portal. Additionally, the research team will conduct internal audits by reviewing automated reports built into the ADAPT Portal to ensure system functioning, correctness and accuracy of data entry.

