#### Secondary outcomes

ADAPT CP secondary outcomes will address the following domains: acceptability, adoption, appropriateness, feasibility, fidelity, cost and penetration, and sustainability of the ADAPT CP, defined in large part by the Proctor framework of implementation outcomes [33] (see detail below and in Table 1). ADAPT implementation strategy outcomes will address similar domains, but with reference to the degree to which implementation strategies (Awareness Campaigns, Champions, Academic Detailing and Support, Education, Reporting and Technology) support the implementation of the ADAPT CP.

*Acceptability is* operationalised as the perception of cancer service staff that the ADAPT CP (1) and the ADAPT implementation strategies (2) are agreeable, palatable and satisfactory, the first in addressing anxiety and depression in their client population, the second in facilitating implementation. This will be measured qualitatively during staff interviews.

*Adoption* of the ADAPT CP (1) is operationalised as the proportion of patients at each site who are registered and screened on the ADAPT Portal. Adoption of the ADAPT implementation strategies (2), is operationalised as mean staff ratings of how much they were aware of, observed and used each implementation strategy, collected via the staff questionnaire.

*Appropriateness* is operationalised as the extent to which staff believe that the ADAPT CP has fit, relevance and compatibility at the level of their setting, their role, and the needs of their consumers, measured quantitatively by the Hands 4 U questionnaire [34] (items adapted to the context of this study) and additional study-developed items within the staff questionnaire. Appropriateness will also be measured qualitatively in staff interviews.

*Feasibility*, operationalised as the extent to which the ADAPT CP is considered feasible by staff of each service, given their different needs and resources, and the degree of individual tailoring required to set up the ADAPT Portal, will be measured qualitatively in semi-structured interviews.

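### The protocol says sites and assessing staff stay blinded to the end of the study, but sites see the strategies that define their arm and several assessment instruments reveal it

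*Protocol article*

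**What the plan says.** The blinding statement is in the protocol article, Study procedures and timeline. Straight after saying that allocation concealment will be preserved, it adds that "both sites and ADAPT Program staff conducting assessments will remain blinded until study completion". It carries no qualification, and no mechanism for keeping the blind is described.

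The same section says that "ADAPT research staff will administer Core versus Enhanced implementation strategies as per randomisation during this period".

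Interventions/groups defines the contrast. Core sites receive "additional support from the ADAPT team only at their request (a passive approach"). Enhanced sites receive the Core strategies plus active engagement, including audit and feedback "summarised and presented face-to-face by research staff to site staff". Table 1 lists further Enhanced-only items, among them "Newsletters emailed to site staff at 2, 4, 6, 9 and 12 months" and "Additional proactive contact with Champions at monthly intervals to discuss progress, provide audit reports and discuss additional implementation strategies as needed".

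Under Secondary outcomes, adoption of the strategies is measured as "mean staff ratings of how much they were aware of, observed and used each implementation strategy".

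**The concern.** Blinding is a safeguard that readers rely on when they judge risk of bias, above all for subjective outcomes. If the protocol claims it and the design cannot deliver it, the claim is likely to pass into the trial report and make the staff-reported comparisons look better protected than they are.

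This trial is especially exposed because the strategies are both the randomised exposure and the subject of several secondary outcomes. Staff who know that they are being actively supported, or who notice that they are not, may answer questions on acceptability, usefulness or readiness accordingly. An interviewer or coder who can tell the arm may probe or classify differently.

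**Working it through.** The document gives no figure for this point, so there is nothing to recompute. The check sets the blinding sentence beside the sections on delivery, data collection and outcomes, for each group said to be blinded.

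**Sites**

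1. What separates the arms. Both get the roadshow, a first poster, a champion, Portal tailoring, monthly written Portal reports and IT support (Table 1). Enhanced sites add repeat posters, five newsletters, monthly champion contact, verbal reports, quarterly Portal configuration reviews and face-to-face presentation of issues from the monthly reports. All of these additions are seen by people at the site.
2. What sites know beforehand. At the recruitment meeting, attended by the service head and by psychosocial, nursing, clinical trial and IT representatives, "the study will be described in detail" (Recruitment: cancer services and staff). The article does not say whether the content of each arm is disclosed there.
3. What sites are asked. Site staff rate their awareness, observation and use of each strategy (Secondary outcomes, adoption). The 6- and 12-month data collection also covers its perceived utility (Study procedures and timeline). An outcome that asks people which strategies they saw presupposes that they are not blinded to strategy.

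Sites therefore cannot be blinded to what they receive.

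**Programme staff who assess**

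1. Research staff deliver the strategies by arm, so the people who deliver are unblinded by definition.
2. ADAPT Program staff complete the contact logs, strategy checklists and observational diaries (text below Table 2). An accurate entry records what was delivered, and so shows the arm.
3. The diaries and contact logs are then coded as qualitative secondary data (Secondary analyses).
4. The 6- and 12-month interviews ask about the strategies received, so the answers can reveal the arm to the interviewer and to anyone who codes the transcript.
5. The baseline interviews concern views of the pathway and readiness. Masking an assessor there is possible.

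Assessor blinding is therefore not credible for the checklists, logs, diaries and later interviews.

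**Outcomes affected**

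| Outcome | Source | Exposure to the problem |
|---|---|---|
| Hypothesis 12 (acceptability, readiness) | Staff report | Direct |
| Hypothesis 11, staff-rated parts | Questionnaire, interview | Direct |
| Hypothesis 11, delivery and fidelity | Checklists and logs kept by programme staff | Recorder knows what was delivered |
| Primary outcome | Extracted from the Portal | Little assessor judgement |

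Power for secondary endpoints anticipates at least 10 staff at each of 12 sites: 10 × 12 = 120 staff as a minimum.

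**The case against.** The best defence is that seeing one's own strategies is not the same as knowing one's arm. Core sites also get posters, a champion and reports, so a site might not realise that it is Core. The clause follows directly on allocation concealment and may have been meant in that narrower sense. But concealment ends at assignment, whereas the sentence runs to study completion. A withheld arm label is not mentioned, and it would protect little when the outcome asks about the strategies themselves.

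A second objection stands. The sentence covers only programme staff who conduct assessments, while the delivery sentence names research staff. A reader might infer that the same individuals deliver and assess. The document does not say so, and a split of duties could sit in the full protocol. The point therefore rests on what the forms and interviews reveal, not on who holds which job.

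A third objection also stands. A reader might infer that the primary outcome is biased because Enhanced sites, coached on Portal statistics, could record the same care more fully. That is a question of measurement and would arise even under perfect blinding. Both arms receive monthly written Portal reports, and the article does not state who enters each pathway component, so a count of staff-recorded components would be inference. Online questionnaires that download automatically also limit assessor influence on the questionnaire data, though not the respondents' own knowledge.

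**Conclusion.** The blinding sentence is wrong as written for sites, and not credible for assessors who use the strategy checklists, logs, diaries and 6- and 12-month interviews. Nothing elsewhere in the article repairs it.

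The consequence is confined mainly to the staff-reported and team-recorded secondary outcomes: hypothesis 12, the staff-rated parts of hypothesis 11, and the qualitative material. Hypothesis 11 is not wholly staff-reported, because delivery and fidelity of the strategies draw on team records. The direction and size of any bias cannot be derived from the document. Neither the sample size nor the primary model has to change.

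The conclusion assumes that the strategies are delivered as Table 1 describes and that no masking procedure exists beyond the one sentence. If the full protocol does provide separate masked assessors, the assessor half of the point narrows to naming them. The site half is unaffected.

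**What to change.** Replace the sentence with three statements:

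- Allocation is concealed up to assignment.
- Sites and the staff who deliver the strategies are not blinded.
- Which staff, if any, are masked, to what, and by what means.

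Then mask what can be masked. Run the Portal adherence scoring and the primary model on coded arm labels, and remove arm identifiers from transcripts before coding where possible. Report hypothesis 12 and the staff-rated parts of hypothesis 11 as unblinded self-report. A table of adherence by pathway component would help readers but is optional.

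The cost is a protocol wording change, coded labels and some transcript preparation. The interventions and the number of sites stay as they are. The downside is that the trial can no longer claim full blinding.
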